### Plans to give access to the full protocol, participant-level data, and statistical code

The datasets and statistical code utilized in the current study, as well as the full protocol, are accessible from the corresponding author upon reasonable request.

### Randomization

Patients are randomly assigned in a 1:1 ratio to the MEFIX or CLOSURE group. Allocation is conducted by computer-generated permuted random blocks (size 4) stratified by 12 hospitals. Block randomization is performed by an independent biomedical statistician using R software. A principal investigator (PI) retains the random assignment tables from each hospital. When eligible patients are recruited from each hospital, the clinical research coordinator (CRC) at the PI’s institution is notified. The CRC then confirms the randomization result on the day prior to the surgery and subsequently informs the respective institution.

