### Assessment of outcomes

#### A) Primary outcome

The number of patients who underwent surgery for bowel obstruction caused by Petersen’s hernia within 3 years after laparoscopic or robotic gastrectomy. The results will be assessed by the PI and an independent biomedical statistician, who collectively compile data from each institution.

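### Allocation concealment is inadequately protected, and knowledge of the arm can influence exclusions after allocation and classification of the primary event

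*Protocol article*

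**What the plan says.** **Sequence and custody (Protocol article, Randomization).** "Allocation is conducted by computer-generated permuted random blocks (size 4) stratified by 12 hospitals". The list is made independently: "Block randomization is performed by an independent biomedical statistician using R software". It then goes to the PI: "A principal investigator (PI) retains the random assignment tables from each hospital".

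**Release (same section).** "When eligible patients are recruited from each hospital, the clinical research coordinator (CRC) at the PI’s institution is notified". Then: "The CRC then confirms the randomization result on the day prior to the surgery and subsequently informs the respective institution".

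**Conditions met only in theatre.** Inclusion criteria list the gastrectomy performed (laparoscopic or robotic) and a B-II or REY reconstruction. Elimination criteria remove participants who did not have the appropriate operation or lack outcome data. Statistical analysis allows patients who were untreated, or have no data after randomisation, to be left out of the intention-to-treat (ITT) analysis.

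**Outcome assessment (Primary outcome).** "The results will be assessed by the PI and an independent biomedical statistician, who collectively compile data from each institution". Only surgery for obstruction due to Petersen's hernia counts. The section on complications says that Petersen's hernia is confirmed by surgical findings and separated from other internal hernias.

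**Blinding.** The trial is called single-blind without naming who is blinded. Data collection says that data collectors are not blinded.

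**The concern.** Three weaknesses sit close together, and each opens a different route to bias.

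1. **Predictability before enrolment.** Surgeons necessarily learn each patient's arm. With a published fixed block of 4 inside each hospital, past assignments carry information about the next one. This bears on concealment itself.
2. **The PI's two roles.** The person who holds every hospital's list also takes part in assessing the primary outcome. Deciding between Petersen's and another internal hernia with the arm known is a detection-bias risk.
3. **Early release.** The surgeon knows the arm while the operation is still being decided, and what is performed determines whether the patient stays in the trial. Conversion, or a reconstruction other than B-II or REY, could lead to removal. This is post-randomisation selection.

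The stake is unusually high because very few primary events are expected.

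**Working it through.** **Inputs.** From Sample size: 1.15% in both arms, margin 3%, one-sided 0.025, power 80%, 199 per arm, 222 per arm and 444 in total after 10% dropout. From Randomization: 1:1, block size 4, 12 hospitals. From Trial status: 159 enrolled at submission.

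**Step 1: the plan's own figures.** n = (1.960 + 0.842)² × 2 × 0.0115 × 0.9885 / 0.03² = 198.3, rounded up to 199. Then 199 / 0.90 = 221.1, rounded up to 222, so 444 in total. All three agree with the article.

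**Step 2: predictability of a fixed block of 4.** There are six equally likely sequences of two A and two B.

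- Certain assignments: the fourth always. The third is certain only if the first two are alike (2 of 6 sequences). Share = (1 + 1/3) / 4 = 33.3%.
- Best-guess success by position: 1/2, 2/3, 2/3, 1. Mean = 2.833 / 4 = 70.8%, against 50% with no information.
- Larger fixed blocks help only modestly: size 6 gives 25.0% and 68.3%; size 8 gives 20.0% and 66.6%.
- With equal recruitment (assumed), 444 / 12 = 37 patients per hospital, of which about 37 / 3 ≈ 12 would be certain.

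These are ceilings. They require a recruiter who knows the block size, tracks every assignment at the hospital in order, and knows the next patient's place in the sequence.

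**Step 3: expected events.** 444 × 0.0115 = 5.1.

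**Step 4: what one event does.** The article compares the upper limit of a two-sided 95% interval for the difference with 3% but names no interval method. A Wald interval is assumed here: upper limit = d + 1.96 × √[p₁(1−p₁)/n + p₂(1−p₂)/n].

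| Per arm | MEFIX vs CLOSURE events | Upper limit | Against 3% |
|---|---|---|---|
| 199 | 3 vs 2 | 2.69% | met |
| 199 | 4 vs 2 | 3.40% | not met |
| 222 | 3 vs 2 | 2.41% | met |
| 222 | 4 vs 2 | 3.05% | not met |

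For 4 vs 2 at 222: d = 2/222 = 0.90%, standard error 1.095%, and 0.90 + 1.96 × 1.095 = 3.05%. Reclassifying one MEFIX event as another internal hernia moves this to the 3 vs 2 row. Excluding that patient instead (3/221 vs 2/222) gives 2.42%, the same conclusion. Another interval method may move the pair of counts at which the result turns.

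**Step 5: when the arm is needed.** The description of the CLOSURE procedure places the mesenteric suture after the anastomosis. The MEFIX suture is located relative to the jejunojejunostomy. Nothing in the description requires the arm to be known before the reconstruction is complete.

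**The case against.** A reader might infer that concealment is lost altogether. The documents do not support that. The sequence is generated independently, and a hospital hears the arm from a central coordinator only after it has recruited the patient. Only the PI, or someone with access to the tables, could know the arm before enrolment, and the article does not say whether the PI enrols or operates on trial patients.

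The other objections, and what stands of each:

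- **The predictability figures are a ceiling.** This stands. Patients are approached at outpatient visits and assigned only shortly before surgery, so several may be waiting at once and the order is blurred.
- **Most eligibility is screened at enrolment.** This stands. Only the operation and reconstruction performed are settled in theatre. B-II and REY both qualify, so choosing between them excludes nobody. The article gives no rate of conversion or other reconstruction, so no number of lost patients can be attached.
- **Table 1 might seem to contradict release the day before.** It does not. Its columns are coarse, and that release fits the column headed Surgery.
- **The endpoint is a reoperation confirmed by operative findings, and the PI shares the assessment.** This limits discretion but does not remove it, since only hernias attributed to Petersen's defect count. It is not stated whether the co-assessing statistician is the one who generated the list.
- **Early release and the PI's assessing role are not concealment failures.** Correct. They are post-randomisation selection and detection bias, and are treated as such here.

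**Conclusion.** The point holds in this form: concealment is inadequately protected, and knowledge of the arm can reach both exclusions after allocation and classification of the primary event. The block design makes up to one third of assignments certain and up to 71% guessable, as a ceiling for a fully informed observer at a hospital. The PI's custody of the lists, together with co-assessment of the outcome, is stated outright. Early release matters because the elimination criteria and the permitted ITT exclusions give it a route to the result.

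No bias is shown to have occurred, and its size cannot be estimated from the article. What can be shown is sensitivity: with about 5 events expected at the planned rate, and a Wald interval assumed, one reclassified or excluded event can reverse the non-inferiority conclusion. The changes are inexpensive and should be made.

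**What to change.** 1. **Custody.** Have the lists held by someone independent of both recruitment and outcome assessment: not the PI, and not the statistician who co-assesses the outcome, since that would only relocate the conflict.
2. **Blocks.** For patients still to be enrolled, use randomly varying block sizes that are not disclosed to the hospitals. At submission 444 − 159 = 285 allocations of the planned total remained (267 if the total of 426 in Trial status is used).
3. **Release.** Have the existing coordinator release the arm once the B-II or REY anastomosis is complete and before the mesenteric suture. If that is not practicable, keep all randomised patients in the ITT set whatever operation was performed, and amend the elimination criteria and the ITT exception accordingly.
4. **Classification.** Have the existing assessors decide between Petersen's and other internal hernia without access to the allocation list. Operative findings may still reveal the arm, so this reduces the risk but does not remove it. It also protects patients already enrolled.

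**Cost.** An intraoperative call to one coordinator from 12 hospitals, whose capacity the article does not describe; a regenerated list for remaining patients; and a change of allocation procedure partway through enrolment, to be dated and reported. The sample size is unchanged.

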### Intervention description

The gastric cancer is diagnosed by preoperative biopsy, endoscopic ultrasonography, or CT. Laparoscopic or robot gastrectomy is performed. Partial omentectomy and D1+ lymph node resection are performed for early gastric cancer (EGC), while total omentectomy and D2 lymph node resection are performed for advanced gastric cancer (AGC). The lymph node resection extent follows the Japanese Classification of Gastric Carcinoma published in 2020 [12]. B-II or REY reconstruction is performed using intracorporeal and antecolic methods. Isoperistaltic or antiperistaltic anastomosis is performed differently depending on the preference of the technician. All technicians send surgical videos to the principal investigator (PI) before patient registration to verify quality control.

#### A) Operative methods for Petersen’s defect closure (CLOSURE group)

The Petersen’s defect, which occurs between the mesentery of the jejunum and transverse colon, is sutured with a nonabsorbable thread after a gastrojejunal or esophageal-jejunal anastomosis. First, a traction suture is performed between the jejunum and transverse colon, and Petersen’s defect is closed continuously using a nonabsorbable barbed suture V-Loc™ 3-0 (Medtronic VR, Minneapolis, MN, USA). Because leaving the tip of the barbed suture can cause bowel obstruction, backward suture with the V-Loc 3-0 was performed two to three times at the last suturing step. Subsequently, the tip is cut short after anchoring (Fig. 3).

**Fig 3 Fig3:**
[figure not shown]
Petersen’s defect closure; CLOSURE group. Petersen’s defect was closed continuously using a nonabsorbable barbed suture between the jejunum and transverse colon

#### B) Operative methods for mesentery fixation (MEFIX group)

The MEFIX method, by fixing the jejunal mesentery to the transverse mesocolon, allows for small bowel herniation. However, it also helps prevent whole bowel ischemia by inhibiting the twisting of the small bowel mesentery.

The arcade artery (blue area, jejunal side) and transverse mesocolon (purple area, colonic side) have relatively few blood vessels under the vasa recta of the jejunal mesentery within 30 cm distal to the jejunojejunostomy site (Fig. 4a). A traction suture is performed at the suture origin, and the mesentery of the jejunum is fixed to the transverse mesocolon with a nonabsorbable barbed V-Loc™ 3-0 suture (Medtronic VR, Minneapolis, MN, USA). It is sutured from the inferior arcade artery to the mesenteric root, which is present in approximately 2/3 of the mesentery of the small intestine. Similarly, in the final suturing step, the reverse suture is performed two to three times with the V-Loc 3-0, and the tip is cut short after anchoring (Fig. 4b).

**Fig. 4 Fig4:**
[figure not shown]
**A** Jejunal mesentery side (blue area) and transverse mesocolon (purple area). Petersen’s defect is outlined in the dotted area. **B** Petersen’s defect closure; MEFIX group. The jejunal mesentery was fixed to the transverse mesocolon using a nonabsorbable barbed suture. JJ, jejunojejunostomy

### Assessment of outcomes

#### A) Primary outcome

The number of patients who underwent surgery for bowel obstruction caused by Petersen’s hernia within 3 years after laparoscopic or robotic gastrectomy. The results will be assessed by the PI and an independent biomedical statistician, who collectively compile data from each institution.

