## Background

Petersen’s hernia was first described in 1900 by Walther Petersen, a German surgeon, following the appearance of an internal hernia after gastrectomy and gastrojejunostomy (GJ) [1]. The space between the mesentery of the small intestine and the transverse colon after the gastrojejunal or esophageal-jejunal anastomosis is called “Petersen’s defect.” In Petersen’s hernia, the mesentery rotates and twists; therefore, an emergency event may occur in which the entire small intestine is necrotic due to impaired blood circulation.

After laparoscopy-assisted distal gastrectomy was first performed in 1994, it has become the standard surgery for early gastric cancer, as reported by Kitano et al. [2]. It is minimally invasive compared with open surgery, which reduces the risk of postoperative adhesions, recovery time of bowel movements, hospital stay, and postoperative pain. However, due to relatively fewer adhesions, the incidence of internal hernias is higher in laparoscopic surgery than with open surgery, and the incidence of Petersen’s hernia after laparoscopic REY gastrojejunostomy is reported to be 1.7–9.7% [3–8]. The anti-adhesive agent, which has been widely used recently, is also thought to be one of the reasons for the increased incidence of internal herniation [9]. According to Blockhuys et al., the incidence of internal hernias decreases when Petersen’s defect closes [10]. Many surgeons also believe that closure of the mesenteric defect with nonabsorbable sutures prevents Petersen’s hernia.

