### Objectives

This study aims to compare the incidence of intestinal obstruction above the Clavien-Dindo classification grade III due to Petersen’s hernia between the MEFIX method and conventional closure methods after minimally invasive surgery such as laparoscopic or robotic gastrectomy.

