### Statistical analysis

All outcomes are assessed using an intention-to-treat analysis that included all patients who were randomly assigned. However, patients who fall under “failure of major entry criteria,” such as those who are not treated at all or do not have available data after randomization, can be excluded from the ITT analysis. Per-protocol analysis also will be performed to evaluate the treatment effect under full compliance.

Demographic data and baseline characteristics of all randomized participants will be pooled. Data will be analyzed using R version 4.2.1 (R: a language and environment for statistical computing, R Foundation for Statistical Computing, Vienna, Austria). Continuous variables will be presented as mean and standard deviation or median and interquartile range. Categorical variables will be described as frequencies and percentages. We will analyze clinicopathological data and postoperative outcomes, including the primary and secondary endpoints, using the chi-square test, Fisher’s exact test, Student’s *t*-test (two samples), or Mann–Whitney *U*-test as appropriate methods based on the type of variables.

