#### B) Detailed complications that occur during the postoperative hospitalization period

Short-term complications are defined within 30 days after surgery and are classified and recorded according to the Clavien–Dindo classification.Post-discharge investigations and long-term complications are as follows:Long-term complications are defined as those occurring 90 days postoperatively.Outpatient follow-up: Occurrence of Petersen’s hernia, other long-term complications, and incidence of readmissionOccurrence of Petersen’s hernia: Petersen’s hernia requires reoperation.

The pathologic Petersen’s hernia is confirmed by surgical findings (i.e., the preoperative hernia is suspected, but hernias in other areas are diagnosed as internal hernias, not Petersen’s hernia). The clinical Petersen’s hernia before surgery is diagnosed through radiologic findings (mesenteric whirling sign, narrowing of superior mesenteric vein and dilated duodenum, etc.) with related symptoms such as nausea or vomiting. Abdominal CT is usually recommended for radiographic examinations. Ultrasonography is possible, but superior mesenteric vessel rotation must be confirmed.

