### Adverse event

An adverse event (AE) refers to any undesirable medical occurrence in a patient that does not have a causal relation with the treatment. Therefore, an abnormal reaction is an unexpected and undesired symptom (for instance, abnormal laboratory test results) or a transient illness occurring independently of the surgery and without obvious causality. The severity of the AEs is assessed using the National Cancer Institute’s Common Terminology Criteria for Adverse Events (NCI-CTCAE), version 4.03, with detailed information being recorded in the patient’s medical record.

Serious AE is defined as a critical anomaly response if as follows: All deaths within 30 days of surgery are reported as significant AEs, regardless of the causality of the surgery. When a causal relationship is present in the study within 30 days of surgery, the following items are reported (i.e., causal relationships are reported separately as defined, probable, and passive): hospitalization due to severe complications or an extended hospitalization period after surgery. If a patient requires reoperation after the initial surgery (specifically, surgery necessitating general anesthesia in the operating room), any permanent or significant impairment related to the surgical procedure is reported. This includes brain lesions resulting in permanent aftereffects that are associated with the surgery.

If severe or medically significant clinical AEs or abnormal laboratory test results occur during or after the clinical trial period, the investigator shall report them to the PI and Clinical Trial Institutional Review Board (IRB) of the testing hospital, regardless of the treatment the patient received. The critical AEs are then reported by the PI to each responsible researcher at the participating institution, who subsequently reports them to the IRB of the affiliated institution.

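### The primary event requires an operation, so a death from Petersen's hernia without surgery is not counted, although the objective is defined by severity

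*Protocol article*

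**What the plan says.** The primary outcome (Assessment of outcomes, A) is "The number of patients who underwent surgery for bowel obstruction caused by Petersen’s hernia within 3 years" of the gastrectomy. The abstract gives the same definition. Under Data collection, B), occurrence of Petersen's hernia is described as a hernia that requires reoperation, and "The pathologic Petersen’s hernia is confirmed by surgical findings". The same section also defines a non-surgical diagnosis: "The clinical Petersen’s hernia before surgery is diagnosed through radiologic findings", together with symptoms. Nothing brings that diagnosis into the primary endpoint.

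The Objectives section is framed differently. The trial is to "compare the incidence of intestinal obstruction above the Clavien-Dindo classification grade III due to Petersen’s hernia", and the abstract's Background says the same. That is a grade of severity, not a record of who was operated on.

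The Background describes the feared course of the hernia: "an emergency event may occur in which the entire small intestine is necrotic due to impaired blood circulation".

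On deaths, the Adverse event section states: "All deaths within 30 days of surgery are reported as significant AEs, regardless of the causality of the surgery". Its last paragraph also sends severe or medically significant events, during or after the trial period, to the principal investigator and the review board. Clinical observations lists mortality among the data collected. For analysis, "All outcomes are assessed using an intention-to-treat analysis that included all patients who were randomly assigned", with exclusions allowed for patients without available data and no imputation.

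**The concern.** An endpoint defined by an intervention misses patients who had the disease event but never received the intervention. Here that is a patient with herniation and bowel necrosis who dies before theatre or is not operated on. A hernia rescued by surgery counts against its arm; one that kills without surgery does not.

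This matters more than usual because of what MEFIX claims. The article says the technique leaves the defect in place, allows partial herniation, and prevents total herniation and ischaemia of the whole bowel. A fatal unoperated necrosis would be direct evidence against that claim, and the primary analysis cannot register it. In a non-inferiority trial, missing true events tends to favour a finding of non-inferiority. With so few events planned, a single one can carry weight.

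**Working it through.** **1. Can a hernia death without surgery be a primary event?** The possible routes, side by side:

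| Handling | Source | Status of the patient |
|---|---|---|
| Operated patients over all randomised | Primary outcome; Statistical analysis | Non-event |
| Treated as lacking outcome data | Elimination criteria; Statistical analysis | May be dropped |
| Cox or Kaplan-Meier | Statistical analysis | Presumably censored (not stated) |

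In no row is the death a failure of its arm.

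**2. Does another listed outcome capture it?** Under Secondary outcomes, bowel condition is assessed at emergency surgery, so it needs an operation. The small bowel obstruction and short-term complication outcomes stop at 30 days. Occurrence of Petersen's hernia by anti-adhesive agent and anastomosis relies on the occurrence definition, which requires reoperation. After day 30, none captures a hernia death without surgery.

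**3. The plan's own sample size.** Inputs from Sample size: 1.15% in both arms, margin 3%, one-sided 0.025, power 80%.

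n = (1.960 + 0.842)² × 2 × 0.0115 × 0.9885 / 0.03² = 198.3, so 199 per arm. For dropout, 199 / 0.90 = 221.1, so 222 per arm and 444 in total. Both stated figures reproduce, and this point does not affect them.

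**4. Expected events.** 199 × 0.0115 = 2.3 per arm; 222 × 0.0115 = 2.6 per arm.

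**5. Effect of one more MEFIX event.** The rule compares the upper limit of the two-sided 95% interval with 3%. The article does not name the interval method. The Wald limit, which matches the sample size formula, is

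p₁ − p₀ + 1.96 × √[p₁(1 − p₁)/n + p₀(1 − p₀)/n].

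Example, 3 v 2 at n = 199: p₁ = 0.01508, p₀ = 0.01005; 0.00503 + 1.96 × 0.01116 = 0.0269.

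| MEFIX v CLOSURE | Wald, 199 | Wald, 222 | Newcombe, 199 | Newcombe, 222 |
|---|---|---|---|---|
| 2 v 2 | 1.96% | 1.76% | 2.69% | 2.41% |
| 3 v 2 | 2.69% | 2.41% | 3.43% | 3.08% |
| 4 v 2 | 3.40% | 3.05% | 4.13% | 3.72% |
| 4 v 3 | 3.08% | 2.77% | 3.70% | 3.33% |

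Under Wald, the expected result of about 2 v 2 survives one more MEFIX event, while 3 v 2 does not. Under Newcombe the crossing comes one event earlier.

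**6. How often is a result one event from the margin?** I summed binomial probabilities at 1.15% in both arms. The chance that the result is non-inferior by Wald and would cease to be with one more MEFIX event is 19% at 199 per arm and 17% at 222.

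**7. Illustrative bias (assumed shares; the documents give none).** Take true hernia rates at the limit, 4.15% v 1.15%, with a share of hernias in both arms fatal without surgery and uncounted. Probability of a false non-inferiority finding at 199 per arm:

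| Uncounted share | Wald | Newcombe |
|---|---|---|
| 0 | 4.4% | 2.2% |
| 10% | 6.8% | 3.2% |
| 20% | 10.5% | 4.7% |
| 30% | 16.1% | 6.8% |

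**The case against.** The strongest defence is that surgical confirmation is deliberate. The article notes that a suspected Petersen's hernia can prove at operation to be another internal hernia. Data collectors are not blinded and the principal investigator helps assess the outcome, so attributing deaths in cancer patients by CT or clinical judgement would add subjectivity to a clean endpoint. This stands as a cost of the change. It does not explain why a death that meets the protocol's own radiologic criteria should not count.

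The defence also limits the point in four ways, and all four stand.

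- A reader might infer that the protocol names fatal hernia as the worst outcome and scores it as a success. No section mentions death from Petersen's hernia. The Background names necrosis, and necrosis that is operated on is counted. Nor is a success stated: the patient may be a non-event, dropped or censored.
- A reader might infer from the 30-day sentence that later deaths go unreported. They do not: mortality is listed as collected data, and severe events during or after the trial are reportable. Six-monthly CT and review of emergency visits would also make many cases visible. These data do not reach the primary endpoint.
- A reader might infer that one case in either arm decides the trial. At 199 per arm, adding a CLOSURE event to 4 v 2 gives 4 v 3 and a Wald bound of 3.08%, so the conclusion does not change.
- Any single event has this leverage when about two are expected per arm. The arithmetic shows fragility, not a measured bias.

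Handling of deaths in the analysis may also be left to a plan not shown. The definition of the primary event is not so left; the article fixes it.

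**Conclusion.** The point holds in a limited form. As written, a death from Petersen's hernia without an operation cannot be a primary event under any handling the article allows, and the endpoint is narrower than the severity-based objective it serves. This is a defect in a stated definition and worth correcting.

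Its size is unknown. The documents give no rate of unoperated hernia death, and it may be low. What can be said is that one uncounted MEFIX death changes the conclusion in some results (3 v 2 to 4 v 2 by Wald, at either 199 or 222 per arm) and not in others (2 v 2 to 3 v 2 by Wald). With a Newcombe interval the crossing comes one event earlier. The false-positive rates in step 7 rest wholly on assumed shares and on true rates at the margin; they show the direction of the effect and should not be read as an estimate.

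**What to change.** Under Assessment of outcomes, A), define the primary event as surgery for bowel obstruction caused by Petersen's hernia, or death attributed to Petersen's hernia without surgery, within 3 years of gastrectomy. Attribution would use the radiologic-plus-symptom criteria already given under Data collection, B), or a post-mortem finding. State that this brings the endpoint into line with the Objectives section.

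Record cause of death through 3 years, report hernia deaths without surgery separately by arm, and give the surgery-only count as a sensitivity analysis.

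The cost is one clause in the definition and a cause-of-death field for later deaths; no section says that follow-up already records this. The few unoperated cases would lack surgical confirmation, and their attribution would be more subjective. The surgery-only sensitivity analysis shows whether the conclusion depends on them. Recruitment was still under way when the article was submitted (Trial status).
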